### Secondary endpoints

*Self-efficacy in health communication*: Change in the mean sumscore of the SE-12 Survey. All items are answered on a numeric scale at 1–10 as well as the option “not relevant”.

*Burnout*: Change in total score for CBI part 2 (seven questions) and part 3 (six questions). All items are answered on a numeric scale from 0 to 4.

*Jobsatisfaction*: Change in the mean sum score of the MTU. All items are answered on a numeric scale 1–7.

Hypotheses will be tested using paired t test in case of normality and Wilcoxon signed rank test in case of non-normality comparing the intervention and control groups.

Data will be collected on the doctors’ age, sex, spoken language at home, years since university degree, job title and prior participation in communication training. Explorative subgroup analysis will be performed stratified by site and doctors’ experience (years since university degree).

A doctor participating in two or more intervention days with a psychologist is considered compliant with the intervention. Doctors’ questionnaires will be evaluated as intention to treat. In case of crossover, per-protocol analysis will be performed as sensitivity analysis. The proportion of missing data in the doctors' questionnaires will be investigated. If the proportion is less than the expected 5%, a complete case analysis will be performed. In case of missing data above 5%, appropriate imputation methods will be applied.

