## Sample size calculation

Approximately 80 out of the around 90 eligible doctors (89%) are expected to participate in the study.

To achieve a power of 80%, a sample size of 2,080 patients (1,040 in each group) will be obtained by sampling 40 clusters (doctors) with 26 patient questionnaires in each group. In total we thus aim to collect 4160 questionnaires. The proportion in the intervention group is assumed to be 0.28 under the null hypothesis and 0.34 [33] under the alternative hypothesis assuming a difference between the group proportions of 0.06. Due to the lack of international consensus in this research area, an absolute change of 6% was agreed upon by mutual consensus in the steering group, as we believe such change would represent a clinical relevant difference for the patients. The proportion in the control group is assumed to be 0.28. The sample size calculation is based on a two-sided Z Test (unpooled) with intracluster correlation (ICC) set at 0.005, and significance level of the test at 0.05.

Each cluster size of 26 completed questionnaires per doctor at baseline and evaluations aligns with the recommendations from the CAT developers [32]. To meet the target we aim to distribute 30–40 questionnaires per doctor. Staff at each outpatient clinic will assist in the process.

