## Secondary outcome measures (doctors)

At baseline and evaluation all participating doctors at the three departments are asked to fill out questionnaires measuring communication self-efficacy, degree of burnout, and job satisfaction.

Self-efficacy in Health Communication (SE-12) consists of 12 questions eliciting healthcare professionals’ perceived self-efficacy in communication with patients. The questionnaire was developed and validated by Axboe et al. [45]. Parts 2 and 3 of the “Copenhagen Burnout Inventory (CBI)” assess work and patient-related burnout, respectively. The questionnaire has been validated in seven types of workplaces, including doctors at a somatic hospital [46]. In the Region of Southern Denmark job satisfaction is measured among 25,000 healthcare workers in a survey every other year, thus offering a large amount of comparable data. Five items on job satisfaction are extracted from the survey for the present study.

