### Primary endpoint

The primary outcome measure is the change in percentage of “excellent” scores measured by the CAT questionnaire on each of the 14 items. All items are answered on a numerical scale from 1 (poor) to 5 (excellent), as well as the option "not relevant". The difference in percentage of "excellent" scores between patients treated by doctors in the intervention and control groups will be analyzed by binary regression using robust variance estimation and taking clustering of patients seeing the same doctor into account. The model will include participating site as a covariate. Due to the randomization and the high number of observations, exchangeability is expected between the patients in the two study groups, and hence, no further covariates are planned in the model. Exchangability will be investigated using standardized differences. A standardized differences > 0.1 indicate imbalance between groups. Effects will be reported on relative and absolute scales as relative risk (RR) and risk differences (RD).

Data will be collected from the patients’ questionnaires on sociodemographic information, years with cancer, disease stage (curable, incurable, unknown), relation to the doctor (first meet or not), and participation or not of relatives at the consultation. Subgroup analysis stratified by site will be performed.

All analyses will be evaluated as intention to treat. The proportion of missing data in the patient questionnaires will be investigated. If the proportion is less than 5%, a complete case analysis will be performed. If missing data exceeds 5%, an imputation analysis will be applied [47].

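### The doctor endpoints are set up as raw change with tests that cannot adjust for baseline; a model using each doctor's collected baseline score would be more precise, by an amount that depends on an unstated correlation

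*Protocol article*

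**What the plan says.** Under *Secondary endpoints*, the protocol article defines all three doctor outcomes as changes:

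- self-efficacy: "Change in the mean sumscore of the SE-12 Survey"
- burnout: "Change in total score for CBI part 2 (seven questions) and part 3 (six questions")
- job satisfaction: "Change in the mean sum score of the MTU"

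The test is fixed in the same section, for a comparison of the two arms: "Hypotheses will be tested using paired t test in case of normality and Wilcoxon signed rank test in case of non-normality comparing the intervention and" (the sentence ends by naming the other arm).

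The baseline scores will be available. The section *Secondary outcome measures (doctors)* states: "At baseline and evaluation all participating doctors at the three departments are asked to fill out questionnaires".

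The only covariate named anywhere is in the patient-level model under *Primary endpoint*: "The model will include participating site as a covariate". That section leaves out further covariates because of randomisation and the large number of patient observations.

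The number of doctors comes from the section *Sample size calculation*, which states: "Approximately 80 out of the around 90 eligible doctors (89%) are expected to participate in the study". The design there is given as "sampling 40 clusters (doctors) with 26 patient questionnaires in each group". No sample size or power is given for the doctor endpoints.

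**The concern.** Subtracting the baseline score gives it a fixed weight of 1. With equal SDs at both times, the weight that minimises the variance of the group comparison is r, which is below 1 for any scale measured with error or subject to real fluctuation. Two things follow. Raw change carries more noise than necessary. And when the groups happen to differ at baseline, raw change removes more of that difference than it should.

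These endpoints carry the whole of the second hypothesis. The number of doctors is capped by the roughly 90 who are eligible, so lost precision cannot readily be recovered by recruiting more at these sites. The reason given for omitting covariates in the patient model, a high number of observations, does not carry over to about 40 doctors per group.

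This differs from the more basic problem that paired tests compare before with after within doctors and do not compare two independent groups. Replacing them with a two-sample test of change would cure that problem and leave this one in place.

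**Working it through.** **Inputs from the article.** 40 doctors per group; 1:1 allocation; two-sided 5% level; all three scales measured at baseline and evaluation.

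**Assumptions, not in the article.** Equal SD at both times (set to 1); correlation r shown from 0.3 to 0.9; a true effect of 0.5 SD for the power figures.

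**The plan's own figure.** The only sample size stated is for the patient endpoint, and it is where the 40 doctors per group come from. Unpooled Z test, 0.28 v 0.34: n = (1.960 + 0.842)² × (0.28 × 0.72 + 0.34 × 0.66) / 0.06² = 928.8. The design effect is 1 + 25 × 0.005 = 1.125, so 928.8 × 1.125 = 1,044.9 per group, against 1,040 stated. Power at 1,040 is 79.8%. The figure reproduces, but says nothing about power for the doctor endpoints.

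**Variance, raw change against baseline-adjusted.**

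- Raw change, per doctor: 1 + 1 − 2r = 2(1 − r)
- Adjusted for baseline, per doctor: 1 − r²
- Ratio, adjusted to raw: (1 − r²) / [2(1 − r)] = (1 + r)/2
- SE of the group difference: √(2 × variance / 40)

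At r = 0.5, the SE is √(2 × 1.00 / 40) = 0.224 SD for raw change and √(2 × 0.75 / 40) = 0.194 SD adjusted.

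| r | Variance ratio | 40 per arm, adjusted, equals this many with raw change | Detectable difference at 80% power, raw v adjusted (SD) | Power for 0.5 SD, raw v adjusted |
|---|---|---|---|---|
| 0.3 | 0.65 | 62 | 0.74 v 0.60 | 46% v 64% |
| 0.5 | 0.75 | 53 | 0.63 v 0.54 | 60% v 72% |
| 0.7 | 0.85 | 47 | 0.49 v 0.45 | 81% v 87% |
| 0.9 | 0.95 | 42 | 0.28 v 0.27 | above 99% for both |

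The third column is 40 divided by the ratio. Detectable differences are 2.80 × SE (normal approximation). Power is from the noncentral t distribution. A simulation of 10,000 trials at each of r = 0.3, 0.5 and 0.7 gave 47% v 64%, 60% v 72% and 82% v 87%.

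**Chance baseline gaps.** The baseline difference between two groups of 40 has SE √(2/40) = 0.224 SD. The chance of a gap above 0.3 SD in either direction is 2 × [1 − Φ(0.3/0.224)] = 18%. Given a gap D (intervention minus control), raw change is off by −(1 − r) × D. For D = 0.3 SD that is 0.21, 0.15, 0.09 and 0.03 SD in magnitude at r = 0.3, 0.5, 0.7 and 0.9.

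In the simulation, with a true effect of 0.5 SD, the trials whose intervention arm started more than 0.2 SD higher gave mean raw-change estimates of 0.28, 0.33 and 0.40 SD at r = 0.3, 0.5 and 0.7. The adjusted estimate averaged 0.50 each time. Over all simulated trials, both estimators averaged about 0.50.

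**The case against.** **Raw change is a valid estimator.** This stands. Under randomisation, a between-group comparison of change is unbiased and keeps its type I error. A reader might infer from the conditional error that the planned endpoint is biased or gives false positives; nothing in the document supports that. The error cancels over randomisations, and what remains is lost precision and an avoidable error in the particular trial that happens to be imbalanced.

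**The comparator is not the test that the article names.** This also stands. The power figures compare a two-sample test of raw change with an adjusted model, whereas the article names paired tests. A reader might take 46%, 60% and 81% as the power of the plan as written; they are not. They show what would still be lost if the paired tests were corrected to a two-sample test and nothing more.

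**The word change does not rule out adjustment.** True: an adjusted model can have change as its outcome and gives the same treatment estimate as one on the evaluation score. No sentence rejects baseline adjustment for the doctors, and the statement on further covariates concerns the patient model. The limitation comes from pairing change endpoints with tests that take no covariate.

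**Covariates may be set out in the predefined analysis plans that the article mentions.** Those plans are not available here. But the article does not leave the method open. It names both tests, and a plan that adjusted for baseline would have to depart from them.

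**The size is assumed.** Correct. Neither r nor the 0.5 SD effect is in the document, and at r = 0.9 the gain is negligible.

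**Conclusion.** The point holds as a matter of precision on the secondary endpoints. The article collects every participating doctor's baseline score and then fixes endpoints and tests that can use it only by subtraction. Relative to a valid two-sample test of raw change, adjustment cuts the variance by 35%, 25%, 15% or 5% at r = 0.3, 0.5, 0.7 or 0.9, assuming equal SDs. At low to moderate r this is a worthwhile gain for about 40 doctors per group; at high r it is not. Adjustment also removes, on average, the (1 − r) × D error that follows a chance baseline gap.

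The primary patient endpoint is not affected. The change should be made because it is cheap and the number of doctors is limited, not because the conclusions would otherwise be invalid.

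**What to change.** Replace both the paired t test and the Wilcoxon signed rank test with a linear model for each doctor scale: SE-12, CBI (parts 2 and 3 handled as the endpoint defines them) and MTU. The outcome can be the evaluation score or the change, since the treatment estimate is the same. The terms are group, the doctor's own baseline score on that scale, and site, because randomisation is stratified by site. Report the adjusted mean difference with its 95% confidence interval. If residuals are clearly non-normal, keep the model and use robust or bootstrap standard errors in place of the switch to a signed rank test.

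No new data are needed. The cost is a few degrees of freedom per model (one for baseline, two for three sites), slightly more analysis work, and a documented change from the published tests, preferably made before outcome data are examined. The same model also provides the between-group comparison that paired tests do not.

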### Randomization

Doctors are randomly assigned to the intervention and control groups in a 1:1 ratio using Research Electronic Data Capture (REDCap) version 13.1.25 and a block size of 2/4. Stratification based on location is implemented to ensure an equal distribution of workload among the psychologists. Stratification will also allow for site comparison in the analysis. The intervention will last 3–4 months at each site, depending on the number of participating doctors.

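### The tests named for the doctor endpoints give no between-arm contrast and cannot carry the stratification factor site; with unpaired tests, omitting site still costs some precision if change differs between sites

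*Protocol article*

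**What the plan says.** The Randomization section of the protocol article makes the doctor the unit of allocation: "Doctors are randomly assigned to the intervention and control groups in a 1:1 ratio". It then adds "Stratification based on location is implemented to ensure an equal distribution of workload among the psychologists" and, as a second purpose, "Stratification will also allow for site comparison in the analysis".

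The Primary endpoint section follows the design. For the patient-rated outcome it says "The model will include participating site as a covariate".

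The Secondary endpoints section does not. All the doctor endpoints are changes from baseline; the first, for example, is "Change in the mean sumscore of the SE-12 Survey". The analysis is then fixed: "Hypotheses will be tested using paired t test in case of normality and Wilcoxon signed rank test in case of non-normality", with the aim of "comparing the intervention and control groups". Site appears for these endpoints only as one of two factors in an exploratory subgroup analysis. No model with covariates is described for them.

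**The concern.** Two things do not fit together.

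First, a paired t test or signed rank test on before-and-after scores asks whether doctors in one group changed. The arms contain different doctors, and the article describes no matching between arms, so a paired test cannot deliver the comparison of intervention with control that the sentence promises.

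Second, the obvious repair is an unpaired t test or rank-sum test on the change scores. That restores the between-arm contrast but still has no place for site. Allocation within site keeps site differences out of the arm contrast, while a test without site leaves them in the error term. The interval is then wider than the design warrants and the type I error falls below 5%.

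At stake is the precision of the doctor endpoints, which rest on about 80 doctors and for which the article states no power. The article gives some reason to think that change could differ by site. One department recruited in summer and two in autumn, and the length of the intervention period at each site depends on the number of doctors there. How large such differences are is unknown.

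**Working it through.** **The plan's own figure.** The article has no standard deviation, target effect or power for the doctor endpoints, so there is nothing to reproduce for them. Its only size calculation is for the primary endpoint, and it reproduces:

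- n per group = (1.960 + 0.842)² × (0.28×0.72 + 0.34×0.66) / 0.06² = 928.8.
- Design effect = 1 + (26 − 1) × 0.005 = 1.125.
- 928.8 × 1.125 = 1,044.9, against the stated 1,040 per group. Power at 1,040 is 79.8%, against the stated 80%.

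That section also supplies the 40 doctors per arm used below.

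**Inputs for the doctor endpoints.**

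- From the article: 40 doctors per arm, three sites, 1:1 allocation within site, two-sided 5% level.
- Assumed: the standard deviation of change is set to 1; a share r of its variance lies between sites, with r from 0 to 20%; sites have 26, 26 and 28 doctors.

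**Half-width of the 95% interval for the between-arm difference in change**

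- Without site: t(0.975; 78) × √(2/40) = 0.445 SD.
- With site: t(0.975; 76) × √(2(1 − r)/40).

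**Power and type I error** come from 8,000 simulated trials for each r under the null and 8,000 under the alternative. The true difference under the alternative is 0.634 SD, which gives 80% nominal power without site. The Monte Carlo standard error is √(0.05×0.95/8000) = 0.24 points for the type I error and √(0.8×0.2/8000) = 0.45 points for power.

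| Site share r | Half-width without site | With site | Excess width | Type I error without / with site | Power without / with site |
|---|---|---|---|---|---|
| 0% | 0.445 | 0.445 | 0% | 5.0% / 5.1% | 80.4% / 80.4% |
| 2% | 0.445 | 0.441 | 1.0% | 4.8% / 5.0% | 79.8% / 80.3% |
| 5% | 0.445 | 0.434 | 2.6% | 4.4% / 4.9% | 80.8% / 82.3% |
| 10% | 0.445 | 0.422 | 5.4% | 4.0% / 5.3% | 80.8% / 83.4% |
| 20% | 0.445 | 0.398 | 11.8% | 2.7% / 4.9% | 82.7% / 88.0% |

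The power difference is therefore nil at r = 0, about 1.5 points at 5%, 2.7 points at 10% and about 5 points at 20%.

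**The test as literally named.** A paired t test in one arm of 40 doctors has half-width t(0.975; 39) / √40 = 0.320 SD. That is narrower than 0.445 SD because it estimates something else, the within-arm change. With no intervention effect but a drift of 0.2, 0.3 or 0.5 SD common to both arms, it rejects in the intervention arm in 23%, 46% or 87% of trials.

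These figures cover the t-test version without baseline adjustment. The rank tests were not computed. The further gain from baseline adjustment depends on the correlation between baseline and follow-up, which the article does not give.

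**The case against.** A reader might infer that the doctor endpoints will certainly have intervals that are too wide, so that real effects are missed. The documents do not support that, for two reasons.

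- The endpoints are changes. Stable differences between departments in burnout or job satisfaction cancel in a change score, so it is not enough that these are workplace measures. Only site differences in change remain in the error term. The article gives no figure for them, and with none there is no loss.
- The quoted tests are paired. Read literally, their interval is narrower, and the risk is a false claim of effect from a trend common to both arms, not a missed effect. The precision argument applies to the between-arm comparison that the sentence says it intends, once an unpaired test is used.

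Both points stand, and they limit the size of the concern.

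It can also be said that the error is conservative, that the estimate is not biased, that a clustered binary model for patients and a test for doctors need not look alike, and that covariates for secondary endpoints are often left to the analysis plan. The first three are fair: the different methods are not in themselves a contradiction. The last carries less weight, because the article does not leave the method open. It names tests that exclude the stratification factor. The exploratory analysis by site does not put site into the main comparison either.

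**Conclusion.** The point holds in a limited form. Allocation is stratified by site, the primary model carries site, and the tests fixed for the doctor endpoints can neither carry site nor, as paired tests, provide the between-arm contrast. The mismatch between a paired test and a between-arm aim is the more serious fault in the sentence, and replacing the tests with unpaired ones would still leave site out.

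The cost of leaving site out is conditional. It is nil if change does not differ between sites and small up to a site share of 5–10% of the variance of change (interval 2.6–5.4% too wide, about 1.5–2.7 points of power). It reaches about 12% in width and 5 points of power only at an assumed share of 20%. These sizes rest on 40 doctors per arm, near-equal sites and the assumed shares. The matter concerns secondary endpoints only and leaves the primary analysis untouched.

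**What to change.** In the Secondary endpoints section, replace the two tests with one linear model per doctor endpoint. Regress the follow-up score, or the change, on arm, site and baseline score, and report the adjusted between-arm mean difference with its 95% confidence interval. With baseline in the model, the arm coefficient is the same whichever of the two outcomes is used. Robust standard errors are optional. The baseline scores are already collected (Secondary outcome measures section). If a rank test is kept as a sensitivity analysis, apply a two-sample rank test stratified by site (van Elteren) to the change scores.

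This one edit supplies the between-arm contrast and brings the doctor analysis into line with the randomisation and the primary model. It changes wording only and needs no new data. Two degrees of freedom go to site and one to baseline, so about 75 remain of about 78. With a site share of zero, the half-width with arm and site in the model is unchanged at 0.445 SD, so including site costs practically nothing even if it turns out not to matter.

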## Methods

### Setting

This study is a randomized, controlled, multicenter study with three participating sites: Vejle Hospital, Aalborg University Hospital, and Zealand University Hospital. Hypotheses are tested by comparing questionnaires before and after the intervention.

Each site has a study coordinator to ensure adherence to the intervention protocol. The project employs seven experienced psychologists (one person-year in total).

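### The secondary endpoints are to be compared between arms with paired tests, which cannot compare two independent, unmatched groups of doctors

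*Protocol article*

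**What the plan says.** The Secondary endpoints section of the Protocol article defines each doctor-level outcome as a change, for example "Change in the mean sumscore of the SE-12 Survey", with corresponding definitions for CBI parts 2 and 3 and for job satisfaction. The test is then fixed as a "paired t test in case of normality and Wilcoxon signed rank test in case of non-normality comparing the intervention and control groups".

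The Randomization section states: "Doctors are randomly assigned to the intervention and control groups in a 1:1 ratio". Blocks are of size 2/4, and the only stratification factor is site. No matching of doctors across arms is described.

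On timing, the section on secondary outcome measures says: "At baseline and evaluation all participating doctors at the three departments are asked to fill out questionnaires". The Setting section says of the study as a whole: "Hypotheses are tested by comparing questionnaires before and after the intervention".

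By contrast, the Primary endpoint section specifies a between-group binary regression that allows for clustering and has site as a covariate.

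**The concern.** A paired t test and a signed rank test both work on one-to-one differences. The sentence names such tests for a contrast between two groups that have no one-to-one link, so the test and the comparison contradict each other. This is not detail left to an analysis plan: a specific method is stated, and it does not fit the design.

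These endpoints carry the whole of the second hypothesis, on communication self-efficacy, job satisfaction and burnout. If the tests are run before against after within each arm, any shift that affects all doctors alike (season, workload, answering the same questionnaire again) could be reported as an effect of the training.

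**Working it through.** **1. What can be paired.** There are two literal ways to carry out the planned test.

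- *Baseline with evaluation, within a doctor.* The data contain this pairing, since the same doctors answer twice. The test then asks whether the mean change in one arm is zero. It contains no contrast between arms.
- *An intervention doctor with a control doctor.* The design creates no such pairs. Randomisation in blocks of 2/4 within site is not matching, and no matched-pair analysis is described. The result would depend on an arbitrary ordering of doctors. If withdrawals, which the protocol allows, left the arms unequal, some doctors could not be paired at all.

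Neither version estimates the randomised effect.

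**2. The plan's own figures.** No sample size or power is given for the secondary endpoints. The sample size for the primary endpoint reproduces:

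- (0.28×0.72 + 0.34×0.66) × (1.960 + 0.842)² / 0.06² = 928.8 per group.
- Design effect 1 + 25×0.005 = 1.125, giving 1,044.9 per group against the stated 1,040. Power at 1,040 is 79.8%.

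This has no bearing on the point beyond supplying the 40 doctors per arm used next.

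**3. Consequence if the test is run within arms.** Inputs: 40 doctors per arm and two-sided alpha 0.05 (from the article); no treatment effect; change scores with SD 1; and a trend δ common to both arms, in SD of the change. The article gives no SD or trend for these scales, so δ is an assumption and is shown as a range.

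The within-arm paired t statistic has noncentrality δ√40, 39 degrees of freedom and critical value 2.02. At δ = 0.3 the noncentrality is 1.90. The two-sample t test on change scores has noncentrality zero whatever δ is, because the trend cancels. Results from 20,000 simulated trials:

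| Common trend δ (SD of change) | Intervention-arm paired test rejects | Intervention significant, control not | Two-sample test on change rejects |
|---|---|---|---|
| 0 | 5% | 5% | 5% |
| 0.2 | 24% | 18% | 5% |
| 0.3 | 46% | 25% | 5% |
| 0.5 | 87% | 11% | 5% |

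The third column is p(1−p), where p is the rejection rate in one arm. It cannot exceed 25%, so the value at 0.3 SD is essentially its maximum. The article does not plan that decision rule; the column only shows what an informal comparison of two within-arm p values would do.

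**4. Efficiency of the two valid replacements.** Assume a true effect of 0.5 SD of the score and a baseline–evaluation correlation r = 0.6; neither is in the article.

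- ANCOVA: SE = √(2(1−r²)/40) = √(2×0.64/40) = 0.179. Power = Φ(0.5/0.179 − 1.96) = 79.8%.
- Change scores: SE = √(4(1−r)/40) = √(4×0.4/40) = 0.200. Power = Φ(0.5/0.200 − 1.96) = 70.5%.

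With the same formulas, power is 65% against 47% at r = 0.3, and 96% against 94% at r = 0.8.

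**The case against.** The strongest defence is that the sentence states its aim, a comparison of intervention with control, and that the endpoints are defined as changes. It may therefore be a misnamed two-sample t test and rank-sum test on change scores, which would estimate the randomised effect. This is plausible and it stands. A reader might infer that the trial will test each arm separately and discard its control group, but the article does not say so. The before-and-after sentence under Setting does not settle it, because that sentence also covers the primary endpoint, which is analysed between groups. The false-positive rates above are therefore conditional on the within-arm reading.

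The defence does not remove the error. Both named tests are paired ones, both make sense for before-and-after data, and neither can do what the sentence says.

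Three further inferences are not supported:

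- A between-arm comparison does not protect against bias from unblinded self-rating. Doctors in both arms know their allocation. What the comparison removes is a trend common to both arms.
- Choosing the test by normality and leaving out site do not in themselves invalidate the analysis. The first is common practice. The second normally costs some efficiency, and covariate detail may sit in the analysis plan, which is not shown.
- ANCOVA's power advantage is no evidence of the error, since it compares two valid methods.

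**Conclusion.** The sentence is wrong as written: the tests it names cannot make the comparison it announces between independent, unmatched groups. That conclusion rests on the text alone and needs no numerical assumption.

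The size of the harm depends on how the sentence would be carried out. Under the within-arm reading, with 40 doctors per arm, the chance of a false training effect in the intervention arm runs from about 5% with no common trend to about 87% with a trend of 0.5 SD of the change. Under the misnamed two-sample reading there is no inflation, and only the wording is at fault. The article does not decide between the two.

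The error is confined to the secondary endpoints. The primary analysis and its sample size are untouched.

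**What to change.** Replace the sentence on hypothesis testing under Secondary endpoints with wording such as:

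*SE-12, CBI part 2, CBI part 3 and job satisfaction at evaluation will each be compared between arms by linear regression (ANCOVA) with arm, the doctor's own baseline score and site as covariates. The adjusted mean difference will be reported with its 95% confidence interval. If residuals are clearly non-normal, a robust or bootstrap interval for the same difference will be used.*

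At minimum, name a two-sample t test or a rank-sum test on change scores. That alone corrects the error; choosing ANCOVA instead is a gain in precision.

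The cost is one sentence. Baseline scores, evaluation scores and site are all part of the planned data, so nothing further has to be collected and the design does not change.
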